## **8.3 Intervention Compliance**

The total number of BA sessions completed per participant and the average duration of sessions will be summarised descriptively.

## **8.4 Adverse events**

Descriptive statistics of AEs will be presented by treatment arm.

## **8.5 Analysis of main trial sub-population**

For the main trial (BASIL+) the inclusion criteria requires a score of  $\geq 5$  on the Patient Health Questionnaire (PHQ-9) at screening, thereby targeting people at risk of clinical depression or with already established depressive symptoms. This criterion emerged from the early experience in the pilot trial where the research team observed that people with very low scores on the PHQ9 did not engage as well with the intervention. We implemented this inclusion criteria for the planned main trial (anticipated recruitment start date February 2021: <http://www.isrctn.com/ISRCTN63034289>). It is with this in mind that the linear regression for the PHQ-9 will be repeated for the subpopulation in the pilot trial that would be eligible for the main trial (i.e. those with a screening PHQ-9 score of five

or more). From these linear regression, 80% confidence intervals for the mean difference will be presented.

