## 4. Trial Objectives

The aims of BASIL-C19 are to:

1. Use a manualised BA focussed collaborative care intervention and practitioner training package for older adults with multiple health conditions who are following UK government social distancing and isolation guidelines due to Covid-19.
2. Establish procedures for recruitment, randomisation, and retention for a definitive trial.
3. Establish an acceptable and deliverable range of assessment procedures for a definitive trial.
4. Estimate parameters for the sample size for a definitive trial.
5. Assess acceptability of the intervention for Covid-19 induced social isolation/self-isolation.

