## **5. Sample Size**

The primary aim of the BASIL-C19 pilot RCT is to test the feasibility of the intervention and the methods of recruitment, randomisation, and follow-up. Sample size calculations are based on estimating attrition and standard deviation of the primary clinical outcome. We proposed to recruit 100 participants. The intervention will be delivered by support workers and we can allow for potential clustering by support worker assuming an intracluster correlation coefficient (ICC) of 0.01 and an average cluster size of 15. The effective sample size is therefore 88. Assuming 15-20% of participants are lost to follow-up (17% in the CASPER trial of older adults[1]), we should have an effective sample size of at least 70 participants. This will allow a completion rate of 80% to be estimated within a 95% confidence interval of  $\pm 8\%$  and reasonably robust estimates of the standard deviation of the primary clinical outcome measure to inform the sample size calculation for a definitive trial[2].

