## **6. Randomisation**

Eligible and consenting participants were randomised using simple randomisation on a 1:1 basis to either the intervention group (BA) or the usual care with signposting group following completion of the baseline questionnaire. A statistician at the York Trials Unit (YTU), not involved with the recruitment of participants, generated the allocation schedule. Randomisation was carried out by YTU's secure randomisation service and participants informed of their group allocation by telephone (confirmed via letter/email).

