## **8.2 Patient Reported Outcomes**

Patient reported outcomes (PHQ-9, GAD-7, De Jong Gierveld Scale, SF-12v2) at baseline, one and three months will be summarised by group. Mean and standard deviation with the number of observations used in each calculation, will be presented (Table 3). In addition, participant's circumstances regarding Covid-19 will be summarised by group for each time point.

Linear regression will be used to explore differences in the PHQ-9 and De Jong Gierveld Loneliness Scale, adjusting for the baseline measure of the score, between groups at one-month and three-months. The mean difference and a 95% confidence interval will be provided. Model assumptions will be checked prior to analysis.

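### Section 8.5 repeats only the PHQ-9 regression in participants who meet the main-trial criterion; PHQ-9 SD, follow-up, session uptake and recruitment yield are planned only for the mixed sample

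*SAP*

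**What the plan says.** Section 4 lists among the aims to "Estimate parameters for the sample size for a definitive trial", and another aim covers recruitment, randomisation and retention procedures for that trial. Section 5 sizes the pilot on attrition and the SD of the primary clinical outcome, and says the SD is meant to feed the definitive trial's sample size. Section 7.1 makes screening, recruitment and follow-up rates and the number and duration of sessions the primary outcomes.

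Section 8.5 then narrows the target population. The main trial (BASIL+) requires a screening PHQ-9 of at least 5, a criterion that arose because the team saw people with very low scores engage less well with the intervention. The analysis planned for that population is that "the linear regression for the PHQ-9 will be repeated for the subpopulation in the pilot trial that would be eligible for the main trial". Its output is the mean difference with an 80% confidence interval.

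The other summaries have no such split. Section 8.2 gives patient-reported outcomes by group and time point, and the matching table shell in section 12.1 has one column per arm only. Section 8.3 summarises sessions and their duration over participants as a whole. No split is given for the rates in section 7.1. The screening PHQ-9 is collected (sections 7.3 and 7.4).

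**The concern.** The plan recognises that the eligible subgroup is the population of interest. It then repeats there the treatment contrast, which the pilot was not sized to estimate, and leaves out the quantities it was sized for or names as primary.

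The effect falls on the use made of the results. Anyone planning or checking the main trial would have PHQ-9 SDs, follow-up rates and session counts that mix people above and below the cut, and no figure for how many of those screened meet the criterion. Session uptake is the clearest case, because the SAP itself says engagement differs at the low end of the scale. That observation is the stated reason for the criterion, yet no planned summary would check it.

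**Working it through.** **Inputs from the SAP.** Section 5: "We proposed to recruit 100 participants"; "assuming an intracluster correlation coefficient (ICC) of 0.01 and an average cluster size of 15"; "Assuming 15-20% of participants are lost to follow-up"; completion rate 80%. Section 6: participants are "randomised using simple randomisation on a 1:1 basis". Section 8.5: cut at a screening PHQ-9 of 5.

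**Assumed, because the SAP gives neither.** The share f of participants with screening PHQ-9 of 5 or more (40%, 60%, 80%), and the shape of the PHQ-9 distribution.

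**Step 1: the plan's own figures.** Design effect 1 + (15 − 1) × 0.01 = 1.14, and 100 / 1.14 = 87.7, which agrees with "The effective sample size is therefore 88". After loss: 87.7 × 0.85 = 74.6 and 87.7 × 0.80 = 70.2, which agrees with at least 70. The half-width for an 80% rate is 1.96 × √(0.8 × 0.2 / n): 7.8 points at n = 100, 8.4 at 88 and 9.4 at 70. The stated 8 points therefore holds on the number randomised (actual or effective), which is the proper denominator for a completion rate. All these figures are for the whole sample.

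**Step 2: what is planned for whom.**

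| Quantity | Whole sample | Screening PHQ-9 ≥5 |
|---|---|---|
| PHQ-9 mean difference, baseline-adjusted | yes (8.2, 95% CI) | yes (8.5, 80% CI) |
| PHQ-9 mean and SD by arm | yes (8.2) | no |
| Follow-up rates | yes (7.1) | no |
| Sessions completed, duration | yes (8.3) | no |
| Share of those screened who meet the criterion | not applicable | no |

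**Step 3: precision in the subgroup.** Number randomised 100f; effective number 87.7f; after 20% loss 87.7f × 0.8. The 95% CI for an SD pooled over two arms uses the chi-square distribution on that last number minus 2 degrees of freedom.

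| f | Randomised | Effective | After 20% loss | Half-width at 80%, points (on effective n) | SD interval, × estimate |
|---|---|---|---|---|---|
| 40% | 40 | 35.1 | 28.1 | 12.4 (13.2) | 0.79 to 1.37 |
| 60% | 60 | 52.6 | 42.1 | 10.1 (10.8) | 0.82 to 1.28 |
| 80% | 80 | 70.2 | 56.1 | 8.8 (9.4) | 0.84 to 1.23 |
| 100% | 100 | 87.7 | 70.2 | 7.8 (8.4) | 0.86 to 1.20 |

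The effective numbers keep the design effect at 1.14. Clusters would be smaller in a subgroup, so these figures are slightly pessimistic.

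**Step 4: effect on the main trial's sample size.** For a fixed difference, N is proportional to SD² without baseline adjustment, and to the residual variance SD²(1 − r²) with it. Each ratio below is the subgroup value over the whole-sample value, by simulation.

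- Correlated gamma-shaped scores, in which spread grows with the mean (mean 5-8, SD 5-5.5, latent correlation 0.5-0.7): follow-up SD ratio 1.00 to 1.15, and SD² ratio 1.00 to 1.33.
- The same family on a wider grid (SD 4.5-5.5, baseline to follow-up correlation 0.5-0.8, screening to baseline 0.8-0.9): baseline-adjusted ratio 1.10 to 1.81.
- Gamma-shaped screening and baseline scores, but follow-up linear in baseline with constant residual variance, as ordinary linear regression (section 8.2) assumes: baseline-adjusted ratio 1.00 to 1.01.

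The answer depends on which model is assumed, and the SAP contains nothing to choose between them.

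**Step 5: recruitment yield.** If a share f of otherwise eligible people meet the criterion, the number to screen rises by 1/f: 1 / 0.8 = 1.25-fold to 1 / 0.4 = 2.5-fold.

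**The case against.** Several points on the other side stand.

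- A reader might infer that the parameters come from a population the main trial will not recruit. They do not: the pilot sample contains the eligible people, and the estimates are diluted by those scoring 0-4 to a degree the SAP does not state.
- The repeated regression is not only an effect estimate. Its residual SD is a by-product, approximately recoverable from the confidence-interval width and the n per arm. What is missing is that it be named as an output, together with the unadjusted SD.
- A reader might infer that the main trial will be undersized by a definite percentage. Step 4 shows that the figure rests on an assumed distribution, and that no effect is among the plausible results.
- A reader might infer poorer retention among low scorers. The SAP reports a team observation about very low scores and engagement with the intervention. It does not extend this to everyone scoring 0-4, and says nothing about retention.
- A reader might infer that the main trial's sample size waits on these outputs. The SAP does not say which estimates are passed on, and describes that trial as already planned, with recruitment anticipated from February 2021.
- Subgroup estimates would be imprecise. At f = 40% the SD interval (0.79 to 1.37 times the estimate) is wider than the SD shift seen in the gamma simulations (1.00 to 1.15), so the table could not establish that the SD differs.

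None of this supplies the missing follow-up, session and yield figures. Nor can they be treated as left to the protocol, since section 8.5 is the SAP's own provision for this population.

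**Conclusion.** The point holds in a limited form. For its declared target population the SAP plans a treatment contrast, and no PHQ-9 SD, follow-up rate, session summary or recruitment yield. Those quantities are planned only for a mixture that includes people the main trial will exclude. That follows from the text and needs no assumption.

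The size of the consequence cannot be fixed from the SAP. For the baseline-adjusted sample size it runs from about none to a material increase, depending on the PHQ-9 distribution. For session uptake, the SAP's own remark gives reason to expect a difference at very low scores, but no figure. For retention there is no evidence either way. The point is worth acting on because the remedy is cheap and serves two of the stated aims, not because harm to the main trial has been shown.

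**What to change.** Add to section 8.5 one descriptive table for screening PHQ-9 of 5 or more, giving:

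- the number and percentage meeting the criterion among those screened and among those randomised, and n by arm;
- PHQ-9 mean and SD by arm at baseline, one month and three months;
- the residual SD from the repeated regression;
- follow-up rates at one and three months with 95% confidence intervals;
- in the BA arm, sessions completed (counting participants with none as zero) and duration, alongside the same figures for scores below 5, so that the engagement observation can be checked.

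State that these are the estimates most relevant to the main trial.

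The work is one extra table with no new assessment, because the PHQ-9 is recorded at eligibility. The percentage among all screened also needs the scores of people screened but not randomised to have been kept, which the SAP does not state. The price is precision: half-widths of about 9-13 points for the completion rate if 40-80% qualify, against about 8 overall. The whole-sample summaries should stay, and the table should carry its intervals so that the smaller numbers are not over-read.

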## 9. SAP amendment log

Please note all changes that are made to the Statistical Analysis Plan following initial sign-off in the box below. Include details of the changes made, any notes/justification for these changes, the new version number if applicable, who the changes were made by, and the date.

| Amendment/addition to SAP and reason for change | New version number, name and date |
|-------------------------------------------------|-----------------------------------|
|                                                 |                                   |
|                                                 |                                   |
|                                                 |                                   |
|                                                 |                                   |

## 12. Appendices

### 12.1 Example tables and figures

Figure 1: BASIL-C19 CONSORT flow diagram

[figure not shown]

Table 2: Patient baseline demographics, as randomised

| Demographic                             |                           | Intervention
(N = XX) | Usual Care
(N = XX) | Total
(N=XX) |
|-----------------------------------------|---------------------------|--------------------------|------------------------|-----------------|
| Age                                     |                           | N=                       | N=                     | N=              |
|                                         | Mean (SD)                 | xx.x (xx.x)              | xx.x (xx.x)            | xx.x (xx.x)     |
| Sex, n (%)                              |                           |                          |                        |                 |
|                                         | Male                      | xx.x (xx.x)              | xx.x (xx.x)            | xx.x (xx.x)     |
|                                         | Female                    | xx.x (xx.x)              | xx.x (xx.x)            | xx.x (xx.x)     |
|                                         | Prefer not to say         | xx.x (xx.x)              | xx.x (xx.x)            | xx.x (xx.x)     |
|                                         | Other                     | xx.x (xx.x)              | xx.x (xx.x)            | xx.x (xx.x)     |
| Ethnicity, n (%)                        |                           |                          |                        |                 |
|                                         | White                     | xx.x (xx.x)              | xx.x (xx.x)            | xx.x (xx.x)     |
|                                         | Black or Black British    | xx.x (xx.x)              | xx.x (xx.x)            | xx.x (xx.x)     |
|                                         | Asian or Asian British    | xx.x (xx.x)              | xx.x (xx.x)            | xx.x (xx.x)     |
|                                         | Other                     | xx.x (xx.x)              | xx.x (xx.x)            | xx.x (xx.x)     |
| †LTC Type, n (%)                        |                           |                          |                        |                 |
|                                         | Diabetes                  | xx.x (xx.x)              | xx.x (xx.x)            | xx.x (xx.x)     |
|                                         | Respiratory Conditions    | xx.x (xx.x)              | xx.x (xx.x)            | xx.x (xx.x)     |
|                                         | Cardiovascular Conditions | xx.x (xx.x)              | xx.x (xx.x)            | xx.x (xx.x)     |
|                                         | Stroke                    | xx.x (xx.x)              | xx.x (xx.x)            | xx.x (xx.x)     |
|                                         | Cancer                    | xx.x (xx.x)              | xx.x (xx.x)            | xx.x (xx.x)     |
|                                         | Osteoporosis              | xx.x (xx.x)              | xx.x (xx.x)            | xx.x (xx.x)     |
|                                         | Neurological Conditions   | xx.x (xx.x)              | xx.x (xx.x)            | xx.x (xx.x)     |
|                                         | Arthritis                 | xx.x (xx.x)              | xx.x (xx.x)            | xx.x (xx.x)     |
|                                         | Chronic Pain              | xx.x (xx.x)              | xx.x (xx.x)            | xx.x (xx.x)     |
| Smoking Status, n (%)                   | I have never smoked       | xx.x (xx.x)              | xx.x (xx.x)            | xx.x (xx.x)     |
|                                         | I currently smoke         | xx.x (xx.x)              | xx.x (xx.x)            | xx.x (xx.x)     |
|                                         | I am an ex-smoker         | xx.x (xx.x)              | xx.x (xx.x)            | xx.x (xx.x)     |
| Alcohol intake (3+ units daily) , n (%) | Yes                       | xx.x (xx.x)              | xx.x (xx.x)            | xx.x (xx.x)     |
|                                         | No                        | xx.x (xx.x)              | xx.x (xx.x)            | xx.x (xx.x)     |
|                                         | Don't know                | xx.x (xx.x)              | xx.x (xx.x)            | xx.x (xx.x)     |
| Post-16 Education, n (%)                |                           |                          |                        |                 |
|                                         | Yes                       | xx.x (xx.x)              | xx.x (xx.x)            | xx.x (xx.x)     |
|                                         | No                        | xx.x (xx.x)              | xx.x (xx.x)            | xx.x (xx.x)     |
| Degree or equiv. , n (%)                |                           |                          |                        |                 |
|                                         | Yes                       | xx.x (xx.x)              | xx.x (xx.x)            | xx.x (xx.x)     |
|                                         | No                        | xx.x (xx.x)              | xx.x (xx.x)            | xx.x (xx.x)     |

**Marital Status, n (%)**

|                    |             |             |             |
|--------------------|-------------|-------------|-------------|
| Single             | xx.x (xx.x) | xx.x (xx.x) | xx.x (xx.x) |
| Divorced/separated | xx.x (xx.x) | xx.x (xx.x) | xx.x (xx.x) |
| Widowed            | xx.x (xx.x) | xx.x (xx.x) | xx.x (xx.x) |
| Cohabiting         | xx.x (xx.x) | xx.x (xx.x) | xx.x (xx.x) |
| Civil Partnership  | xx.x (xx.x) | xx.x (xx.x) | xx.x (xx.x) |
| Married            | xx.x (xx.x) | xx.x (xx.x) | xx.x (xx.x) |

**Number of Children, n (%)**

|    |             |             |             |
|----|-------------|-------------|-------------|
| 0  | xx.x (xx.x) | xx.x (xx.x) | xx.x (xx.x) |
| 1  | xx.x (xx.x) | xx.x (xx.x) | xx.x (xx.x) |
| 2  | xx.x (xx.x) | xx.x (xx.x) | xx.x (xx.x) |
| 3  | xx.x (xx.x) | xx.x (xx.x) | xx.x (xx.x) |
| 4+ | xx.x (xx.x) | xx.x (xx.x) | xx.x (xx.x) |

**Current circumstance, n (%)**

|                                          |             |             |             |
|------------------------------------------|-------------|-------------|-------------|
| Social/physical distancing               | xx.x (xx.x) | xx.x (xx.x) | xx.x (xx.x) |
| Self-isolating without Covid-19 symptoms | xx.x (xx.x) | xx.x (xx.x) | xx.x (xx.x) |
| Self-isolating with Covid-19 symptoms    | xx.x (xx.x) | xx.x (xx.x) | xx.x (xx.x) |
| Shielding                                | xx.x (xx.x) | xx.x (xx.x) | xx.x (xx.x) |
| Other                                    | xx.x (xx.x) | xx.x (xx.x) | xx.x (xx.x) |

**How many people do you share your home with?, n (%)**

|                  |             |             |             |
|------------------|-------------|-------------|-------------|
| Live alone       | xx.x (xx.x) | xx.x (xx.x) | xx.x (xx.x) |
| 1 person         | xx.x (xx.x) | xx.x (xx.x) | xx.x (xx.x) |
| 2 people         | xx.x (xx.x) | xx.x (xx.x) | xx.x (xx.x) |
| 3 people         | xx.x (xx.x) | xx.x (xx.x) | xx.x (xx.x) |
| 4 or more people | xx.x (xx.x) | xx.x (xx.x) | xx.x (xx.x) |

**Adherence to UK Government's guidance in relation to Covid-19 restrictions, n (%)**

|                      |             |             |             |
|----------------------|-------------|-------------|-------------|
| All of the time      | xx.x (xx.x) | xx.x (xx.x) | xx.x (xx.x) |
| Most of the time     | xx.x (xx.x) | xx.x (xx.x) | xx.x (xx.x) |
| Some of the time     | xx.x (xx.x) | xx.x (xx.x) | xx.x (xx.x) |
| A little of the time | xx.x (xx.x) | xx.x (xx.x) | xx.x (xx.x) |

None of the time

xx.x (xx.x)

xx.x (xx.x)

xx.x (xx.x)

†Not mutually exclusive, participants may have more than one LTC

Table 4: Patient reported outcome measures

| Outcome Measure                                        | Intervention   | Control        |
|--------------------------------------------------------|----------------|----------------|
| PHQ-9, n, mean (SD)                             |                |                |
| Baseline                                               | n, xx.x (xx.x) | n, xx.x (xx.x) |
| 1-month                                                | n, xx.x (xx.x) | n, xx.x (xx.x) |
| 3-month                                                | n, xx.x (xx.x) | n, xx.x (xx.x) |
|                                                        |                |                |
| GAD-7, n, mean (SD)                             |                |                |
| Baseline                                               | n, xx.x (xx.x) | n, xx.x (xx.x) |
| 1-month                                                | n, xx.x (xx.x) | n, xx.x (xx.x) |
| 3-month                                                | n, xx.x (xx.x) | n, xx.x (xx.x) |
|                                                        |                |                |
| De Jong Gierveld Loneliness Scale, n, mean (SD) |                |                |
| Baseline                                               | n, xx.x (xx.x) | n, xx.x (xx.x) |
| 1-month                                                | n, xx.x (xx.x) | n, xx.x (xx.x) |
| 3-month                                                | n, xx.x (xx.x) | n, xx.x (xx.x) |
|                                                        |                |                |
| SF-12v2, n, mean (SD)                           |                |                |
| Baseline                                               | n, xx.x (xx.x) | n, xx.x (xx.x) |
| 1-month                                                | n, xx.x (xx.x) | n, xx.x (xx.x) |
| 3-month                                                | n, xx.x (xx.x) | n, xx.x (xx.x) |
